**Discussion:**

Patients with central nervous system lesions have received tDCS as a painless, non-invasive, easily applied and effective therapy for several decades, and there has been some evidence in recent years showing partial improvement on the level of consciousness of partial patients with DOC. However, reports mainly focus on the patients in a minimally conscious state (MCS), and there is a lack of large-sample clinical trials. This protocol presents an objective design for a randomized controlled trial that aims to study the effectiveness of conventional rehabilitation combined with tDCS therapy for DOC after TBI, to evaluate its safety, and to explore effective and economical therapeutic methods.

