tDCS is a non-invasive brain stimulation technology, which is safe, simple to operate and economical. A previous study [19] has shown that there is no significant untoward effect of tDCS in healthy individuals except for mild tingling (76%), itching (68%), mild burning (54%), and mild pain (25%). tDCS is gradually being applied for treatment of people with motor skills and language impairment after craniocerebral injury, dysphagia, Alzheimer’s disease, Parkinson’s disease, acute and chronic pain, tinnitus, depression and normal subjects, and DOC, as well as in studies such as being tested in healthy individuals [11]. A constant, weak direct current (DC) can effectively pass through the skull and induce bipolar, polarity-related changes through skull conduction on the corresponding cortex. The stimulation effect is determined by the stimulation site, the current intensity, the polarity, and the area of the electrode slice. tDCS works by regulating the activity of spontaneous neuronal networks [12]. At the neuronal level, tDCS regulates excitability in the cerebral cortex. This is mainly due to changes in the polarity of the stimulus, resulting in changes in resting membrane potential depolarization or hyperpolarization, thereby affecting cortical excitability changes in spontaneous neuronal activity. Stimulation usually increases the excitability of the cerebral cortex, and cathodal stimulation reduces the excitability of the cortex [13]. tDCS also increases synaptic plasticity. Besides, some studies have suggested the electrophysiological mechanisms [20–22] and biochemical mechanisms [23, 24] of tDCS, which makes tDCS in DOC more feasible. Nevertheless, clinical research into tDCS combined with conventional rehabilitation in DOC after TBI is rarely reported.

Therefore, the objective of this large-sample, randomized controlled trial is to (1) research the efficacy of conventional rehabilitation combined with tDCS in DOC after TBI; (2) evaluate the safety of tDCS in patients with DOC after TBI; and (3) present the study protocol, the previous results of the clinical trial, ensuring adherence and compliance with the guidelines previously proposed.

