### Sample size

The sample size calculation is based on improvement in scores on the Glasgow coma scale (GCS). According to similar published articles [25], the GCS scores after active tDCS and sham tDCS are respectively (12.44 ± 2.51) and (10.43 ± 1.90), *n* = 38. According to a similar study [26], treatment with conventional rehabilitation combined with tDCS can probably improve the GCS by 2.01 points on average in participants receiving this intervention compared to those in the control group. Improvement will be measured according to the same sample size of the estimation formula:
$$ n=2\left[{\left({u}_a+{u}_{\beta}\right)}^2{\sigma}^2\right]/{\delta}^2 $$

With a type I error of 5% (*α* = 0.05) and 90% power (*β* = 0.10), the estimated required sample size is 33 participants per group. Allowing for a 20% dropout rate during the study, a minimum total of 80 participants is needed to reach the target of 40 participants per group.

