### Statistics methods

#### Statistical analysis

SPSS21.0 software will be used to analyze the test results. In the descriptive analysis of the sample, continuous variables will be expressed by mean and standard deviation for normally distributed data, and median and interquartile range for non-normally distributed data. Normally distributed data variables will be statistically compared between groups using the *t* test. Ordinal-level variables with a non-normal distribution will be statistically compared between groups using the Mann–Whitney *U* test. Measures with a discrete distribution will be expressed as percentages and analyzed using the chi-squared (χ2) or Fisher’s exact test as appropriate. A general linear model or logistic regression model will be applied to adjust for confounding influences if necessary.

We will compare baseline characteristics between groups using the *t* test or Mann–Whitney test for continuous variables and the Pearson chi-squared or Fisher’s exact test for categorical variables. If statistical significance appears, the inequality factors will be treated as confounding variables in the final efficacy analysis. For comparison of the primary or secondary outcomes between groups, the *t* test or non-parametric tests will be used to analyze continuous data, and the Pearson chi-squared or Fisher exact test to analyze categorical data. To control for possible confounding variables, linear models or linear regression will be applied for dependent continuous variables and logistic regression models for dependent categorical variables. Subgroup analysis of the primary outcomes will be stratified by participants’ sex. Analysis of variance will be used for the repeated measurement data. Analysis of the primary and secondary outcomes will be on an intention-to-treat (ITT) and a per-protocol (PP) basis. The result of the ITT analysis will be compared with that of the PP analysis to determine whether the results are consistent. Missing data will be handled according to the method of last observation carried forward. Adverse events will be listed and analyzed using the chi-square test or Fisher’s exact test.

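### The only between-group analysis fixed for the safety objective is a chi-square or Fisher test of adverse events, which at about 40 per arm cannot support a safety statement unless the harm is large

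*Protocol article*

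**What the plan says.** The second numbered objective, at the end of the Background, is to "evaluate the safety of tDCS in patients with DOC after TBI". The abstract's discussion repeats the aim: "to evaluate its safety, and to explore effective and economical therapeutic methods".

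Under Statistical analysis, the sentence that deals with safety is "Adverse events will be listed and analyzed using the chi-square test or Fisher", followed by the rest of the exact test's name. A general rule in the same section also applies: "Measures with a discrete distribution will be expressed as percentages and analyzed using the chi-squared". So per-arm percentages can be expected beside the listing and the test. No risk difference, interval, margin or upper bound is stated for adverse events.

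The Sample size section rests on the Glasgow Coma Scale (GCS) alone. It says that the treatment "can probably improve the GCS by 2.01 points on average", that "the estimated required sample size is 33 participants per group", and that "a minimum total of 80 participants is needed to reach the target of 40 participants per group". It gives no power or expected rate for harms. The only event rates in the article are mild sensations in healthy people (Background).

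**The concern.** A test of no difference can flag a large harm. It cannot show that harm is absent, and its failure to reject says little when the sample was sized for something else. Here the p-value is the only comparative result that the article fixes for a stated objective.

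If active tDCS raised the rate of an uncommon but important event by 5 to 15 points, the planned comparison would more often than not be non-significant. A report of no significant difference in adverse events would then sit beside an objective on safety, with nothing in the stated analysis to show how large an excess the data still allow.

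**Working it through.** **Inputs from the protocol article.** 40 per arm, 1:1 allocation, 20% dropout, type I error 5%, power 90% for GCS, GCS difference 2.01, SDs 2.51 (active) and 1.90 (sham).

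**Assumed.** The adverse-event rates (none are given for these patients), a two-sided 5% level for the adverse-event test, and uncorrected Pearson chi-square when all expected counts are at least 5, with Fisher's exact test otherwise.

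**1. The plan's own figure.** n = 2(u_α + u_β)²σ²/δ² = 2 × (1.960 + 1.282)² × 2.51² / 2.01² ≈ 32.8, so 33 per group. This reproduces the stated number with a two-sided 5% level and the larger SD (one-sided gives 27). Then 33 × 1.2 = 39.6, so 40. After 20% dropout, 40 × 0.8 = 32 remain. Nothing in this calculation concerns harms.

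**2. Chance that the test misses a true excess.** I summed the product of the two binomial probabilities over all pairs of event counts that are not significant.

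| Sham vs active (assumed) | Missed, 40 per arm | Missed, 32 per arm |
|---|---|---|
| 1% vs 5% | 99% | 99.7% |
| 2% vs 10% | 89% | 95% |
| 5% vs 15% | 78% | 87% |
| 5% vs 20% | 52% | 68% |
| 10% vs 25% | 57% | 68% |
| 10% vs 30% | 37% | 49% |
| 5% vs 30% | 12.5% | 26% |
| 10% vs 40% | 9.9% | 17% |

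**3. Active-arm rate needed for 80% power, 40 per arm.**

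| Sham rate | Fisher throughout | Chi-square throughout | Rule above |
|---|---|---|---|
| 0% | 19.5% | 13.5% | 19.5% |
| 5% | 29.5% | 26.5% | 27.5% |
| 10% | 38% | 35.5% | 35.5% |

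The detectable excess is therefore about 14 to 20 points from a zero sham rate, 21.5 to 24.5 points from 5%, and 25.5 to 28 points from 10%.

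**4. Significance against 0/40.** The two-sided Fisher p-value for x/40 vs 0/40 is 2 × C(40,x)/C(80,x).
- x = 6: 2 × 3,838,380/300,500,200 = 0.026
- x = 5: 2 × 658,008/24,040,016 = 0.055
- x = 3: 2 × 9,880/82,160 = 0.24

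Six events (15%) on active are needed.

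**5. What intervals would show.** Newcombe 95% intervals for active minus sham:

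| Active vs sham | Fisher p | Difference (95% CI), points |
|---|---|---|
| 3/40 vs 0/40 | 0.24 | +7.5 (−2.5 to +19.9) |
| 4/40 vs 2/40 | 0.68 | +5 (−8 to +19) |
| 6/40 vs 2/40 | 0.26 | +10 (−4 to +25) |

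With 0/40 on active, the exact two-sided 95% upper limit is 1 − 0.025^(1/40) = 8.8%.

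**The case against.** Listing adverse events and comparing arms by chi-square or Fisher is conventional and valid for such data. The article mentions a predetermined statistical analysis plan that is not shown, and interval methods and table layouts commonly belong there. Safety is also watched in other ways: events are recorded throughout treatment, the Ethics Committee reviews serious events, serious adverse reactions end the test, and a monitoring committee audits the study. The Discussion itself calls the sample small.

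Much of this stands, and it rules out several stronger readings that a reader might infer:

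- *That the trial will treat non-significance as proof of safety.* No section says so, and no safety hypothesis, margin or success rule is stated.
- *That a significance test is all that is planned.* A listing and per-arm percentages are planned too, and a reader could compute a risk difference from them.
- *That the test misses most clinically relevant harms, or any doubling or tripling of risk.* This depends on rates that the article does not give. At 40 per arm, 10% vs 30% is detected more often than not, and 5% vs 30% or 10% vs 40% is missed only about 10% to 13% of the time.
- *That the missing interval is an error in itself.* It may stand in the unseen analysis plan.

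What the objection does not remove is that the article already commits a stated objective to one comparative method, and that method is poorly suited to it at this sample size. Oversight of individual cases is not an analysis that answers the objective. Two bare percentages do not say how large an excess remains possible.

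**Conclusion.** The point holds in a limited form. For the safety objective, the one between-group analysis fixed in the article is uninformative for differences below roughly 20 to 25 points at 40 per arm, or below about 14 to 20 points if sham patients have no events. From a sham rate of 10% or with 32 per arm, the threshold is somewhat higher. A non-significant result could not support a statement that tDCS is safe.

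The size rests on assumed event rates and a two-sided 5% level. The finding concerns what the stated test can deliver, not how the investigators intend to read it. The efficacy comparison is unaffected. The change should be made because without it the safety objective has no interpretable comparative answer in the stated plan.

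**What to change.** In the Statistical analysis section, make estimation the basis of the safety objective:

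- Count each patient once. For any adverse event, any serious adverse event and each event of interest (seizure or skin lesion, for example), report the number and percentage per arm.
- Give the active-minus-sham risk difference with a 95% Newcombe or exact interval, naming the method in advance, and the exact upper limit where no events occur.
- State that the safety conclusion rests on the upper limit of the interval, meaning the largest excess not ruled out, and that a non-significant p-value is not evidence of safety. The chi-square or Fisher test may stay as a descriptive flag.

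This takes one or two sentences and a few table columns from data already being collected, with no extra patients or visits. The real cost is a less favourable safety statement, because the wide upper limit will be on view.

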## Discussion

As a new method in brain function research and treatment, tDCS is painless, noninvasive, easy to apply, and effective. At present, it has been studied and applied in the fields of depressive brain dysfunction [36], Parkinson’s brain dysfunction [37], epilepsy brain dysfunction [38–41], post-stroke brain dysfunction [42, 43], addiction brain dysfunction [44, 45] etc., but has rarely been used in the study of patients with consciousness disorder after TBI.

Studies have shown that transcranial electrical stimulation may regulate brain function by activating the corresponding cerebral cortex through the electrical current [46] and changing the concentration of certain chemicals [47]. In addition, a study also found that tDCS causes a significant increase in cerebral blood volume (CBV) and cerebral blood flow (CBF) and a decrease in the average mean transit time (MTT), which suggests better oxygen delivery to the tissues [48]. This may be one of the physiological ways in which tDCS improves disturbances in consciousness.

tDCS regulates the synaptic microenvironment, such as by altering the mediation of N-methyl-D-aspartate receptor at synaptic level on long-term potentiation and long-term inhibition processes. Studies have also shown that the involvement of tDCS at the synaptic level is also involved in the modification of gamma-aminobutyric acid and dopaminergic and other protein systems [49]. There is also an immediate effect in tDCS, and studies have shown that tDCS can stimulate changes in regional cerebral blood flow. Anodic stimulation of tDCS can induce the increase of cerebral blood flow in the related areas, and the increase may be up to about 17.1%. When the stimulation stops, the blood flow returns to baseline level. When the cathodic stimulation stops, the blood flow increases by about 5.6%. When the stimulation stops, the blood flow decreases by about 6.5% compared with the baseline, and it lasts to the later stage of stimulation. A study [50] on functional MRI and positron emission scanning found that tDCS in the M1 region could lead to the intensification of other regions besides the M1 region, and tDCS could also affect the activity of neurons in thalamus region. Thus, although tDCS acts in the cerebral cortex, it is likely to affect other brain tissues through the interconnection of neurons. It has also been shown that tDCS stimulation of the F3 position using the EEG 10/20 system can increase the blood flow perfusion in the DLPFC and decrease the function of bilateral thalamic blood flow, suggesting that tDCS may be involved in regulating the functional connection between the DLPFC and the thalamus. Thibaut et al. [51] found that when tDCS is used to stimulate the dorsolateral left prefrontal lobe, the left DLPFC, thalamus and anterior wedge lobe increased in the tDCS-positive subjects. This may be a mechanism to improve the awareness of tDCS disturbances.

The double-blind test design was adopted to ensure the authenticity of the test results. In addition, the GCS, GOS, EEG, BAEP, and USEP were selected as evaluation indexes using the scale score and electrophysiological measurement, so as to comprehensively and objectively evaluate change in the patient’s consciousness disorder. DOC after brain injury makes the prognosis worse and brings a great burden to the family and society. The purpose of this protocol is to investigate the effects of tDCS in patients with DOC after brain injury and to find a new intervention to improve this condition. Finally, as this trial is based on a small sample, it would be of great value to conduct a meta-analysis of the results from other similar studies. Thus, it will provide new medical evidence on the use of tDCS in patients with DOC after TBI, which is one aspect of our future research work.

### Trial status

This protocol version number is V2.1(2019082201). Participant enrollment will start in December 2019. The trial is expected to be completed by the end of December 2020.

## Data Availability

All data will be archived in an electronic CRF under the responsibility of the First Affiliated Hospital of Nanchang University. The data set generated and analyzed during the current study will be available from the corresponding author on reasonable request.

## Abbreviations

AE: Adverse event
BAEP: Brainstem auditory evoked potential
CRF: Case report form
DBS: Deep brain stimulation
DLPFC: Dorsolateral prefrontal cortex
DOC: Disorders of consciousness
DRS: Disability Rating Scale
EEG: Electroencephalogram
GCS: Glasgow Coma Scale
GOS: The Glasgow Outcome Scale
ICU: Intensive care unit
ITT: Intention to treat
MCS: Minimally conscious state
MNES: Median nerve electrical stimulation
MRI: Magnetic resonance imaging
NICU: Neurologic intensive care unit
PP: Per protocol
TBI: Traumatic brain injury
tDCS: Transcranial direct current stimulation
USEP: Upper sense evoked potential
UWS: Unresponsive wakefulness syndrome
VNS: Vagus nerve stimulation
VS: Vegetative state
